**Discussion:**

The ANC study is based on an original methodology, the stepped wedge trial design, which is appropriate for evaluating the implementation of a geriatric and nutritional assessment during the perioperative period. We describe the purpose of this geriatric intervention, which is expected to apply the ESPEN and SFNEP recommendations through the establishment of an undernutrition screening and a management program for patients with cancer. This intervention should allow a decrease in patient morbidity and mortality due to undernutrition.

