## Background

Colorectal cancer has the third highest incidence of cancer and the second highest mortality. The incidence and mortality curves significantly increase after the age of 55 years, with patients over 70 years old representing 60.5% of the incidence cases and 75.2% of cancer deaths [1, 2].

While the rates of perioperative morbidity and mortality have been drastically reduced in older patients due to the use of better anesthetic and post-surgical intensive care techniques [3, 4], age remains associated with a decrease in overall survival. The main mortality risk factors have recently been evaluated using a multivaried analysis and this predictive model has been prospectively validated on a test sample population [5]. The authors confirmed that the primary mortality risk factor is age: the risk is 1.8-fold higher between 80 and 85 years while beyond 90 years it is almost 3-fold higher. The increased rate of mortality in older patients compared to younger ones appears to be limited to the early postoperative period, as the disease specific survival ratio after this time is similar to that expected from the age-matched population as a whole [6]. The condition of the perioperative care therefore represents a priority for the improvement of colorectal cancer prognosis in older patients [7–11].

Beyond all the factors that affect the postoperative morbidity and mortality, the nutritional state of the patient is the most important [12]. Undernutrition significantly increases postoperative morbidity-mortality and is responsible for an increase in infectious and non-infectious postoperative complications and in the toxicity linked to the chemotherapy or radiotherapy treatment, leading to a prolongation of patient hospitalization and to an alteration of their quality of life [13].

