propose an adapted preoperative nutritional management according to the nutritional status of the patient using the decision tree for nutritional care [20];advise the surgery team of the nutritional recommendations to follow in the postoperative phase (Fig. 1).

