### Outcome and measurement

The primary outcome measure is to determine the impact of the geriatric intervention on the level of perioperative nutritional management, in accordance with the current European guidelines, of patients aged 70 years old or above who are undergoing surgery for colorectal cancer. This will be accomplished by evaluating the percentage of patients having received a nutritional screening i.e. measurement of body weight and size, calculation of the body mass index (BMI), evaluation of a recent body weight loss and an albumin assay at least 7 days before surgery, and having received oral immunonutrition during 7 days before surgery (if absence of malnutrition) or immunonutrition during 7 days before and 7 days after surgery (if moderate malnutrition) or artificial nutrition during 7–14 days before surgery and 7 days after surgery.

The secondary outcomes are:The percentage of patients having received a nutritional screening, i.e. measurement of body weight and size, calculation of the body mass index (BMI), evaluation of a recent body weight loss and an albumin assay at least 7 days before surgery.The percentage of patients having received oral immuno-nutritionThe percentage of patients with undernutrition, severe undernutrition and cachexiaThe rate and type of postoperative complications, from grade I to V, according to the Common Terminology Criteria for Adverse Events v4.0 (CTCAE) of National Cancer Institute, occurring up to 30 days after surgery.The number of actual oral nutritional supplements intakes with respect to planned ones (noted in the patient diary given at the preoperative geriatric assessment).The comparison of functionality scores obtained on the ADL and IADL, evaluated by the GT between the beginning (between 14 and 7 days before surgery) versus the end (after surgery, the day before or the day of discharge from the surgical ward) of the hospitalization period.The emotional state of the patient evaluated with the mini-GDS (score on 4) and the GDS 15 (if mini GDS score >2).The number of concomitant treatments (number of drug specialties between 0 and 3, between 3 and 6, over 6) during the hospitalization period.

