Globally (without taking into account the intervention) will be described:* malnourished subjects, malnourished subjects who could not get a prescription for nutritional management, severe malnourished patients, cachectic subjects among all subjects who underwent screening (percentage and 95% confidence interval)* the emotional score, the mini GDS on subjects who received screening, the number of concomitant treatments and specialties, the number of food intake on the number of prescribed taken, the average change in IADL score (mean, standard deviation, median, minimum, maximum).

The percentage of complications will also be compared between subjects who received nutritional support and those who don’t have benefited of this support by a Chi square test.

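### The one complication comparison the article describes groups patients by nutritional support received, not by randomised phase, so it is confounded and cannot show whether the intervention reduces morbidity

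*Protocol article*

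**What the plan says.** Postoperative complications are a secondary outcome (Outcome and measurement): rate and type, CTCAE grades I to V, "occurring up to 30 days after surgery". Their analysis comes at the end of the Statistical analysis section: "The percentage of complications will also be compared between subjects who received nutritional support" and those who did not, by a Chi-square test. That sentence does not define nutritional support.

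Elsewhere in the same section, the primary endpoint is compared by intervention or control group with time in a generalized linear mixed model (GLMM). Screening and care prescription are also compared by GLMM. The article describes no such comparison for complications.

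On who gets support, the geriatric team is to "propose an adapted preoperative nutritional management according to the nutritional status of the patient" (ANC program). The regimens counted in the primary outcome differ by status: preoperative immunonutrition only if there is no malnutrition, "immunonutrition during 7 days before and 7 days after surgery (if moderate malnutrition"), and otherwise "artificial nutrition during 7–14 days before surgery and 7 days after surgery".

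On prognosis, the Background states: "Undernutrition significantly increases postoperative morbidity-mortality and is responsible for an increase in infectious and non-infectious postoperative complications". On what is expected, the Abstract says: "This intervention should allow a decrease in patient morbidity and mortality due to undernutrition". The Discussion of the intervention says much the same.

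**The concern.** In a stepped wedge trial, randomising the order of crossover protects comparisons between control and intervention phases. It does not protect a comparison between patients who did and did not receive support. Receipt is decided after inclusion and may depend on nutritional status, center, calendar period and time available before surgery. An unadjusted Chi-square handles none of these.

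The article expects the intervention to lower morbidity. A reader of the results will look to the complication analysis for evidence, and the comparison described cannot supply it: a difference could appear in either direction with no effect of support, and a null result could hide an effect.

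**Working it through.** **1. Inputs from the article.** 5 centers, 6 periods, 5 patients per center-period (150 in all); guideline-concordant management 5% in control and 20% in intervention; coefficient of variation (CV) between centers 0.15 to 0.40; alpha 5% (taken as two-sided); undernutrition up to 50% in older hospitalised patients (Background). No complication rate is given, so every complication and uptake rate below is an assumption.

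**2. Support is tied to phase.** With one center crossing at each step there are 15 control and 15 intervention cells, or 75 patients each. If support means guideline-concordant management, the planning rates give 75 × 0.05 + 75 × 0.20 = 3.75 + 15 = 18.75 supported patients. Of these, 15/18.75 = 80% are in the intervention phase. Among the unsupported, 60/131.25 = 46% are. The groups therefore differ in period and center mix before nutritional status is considered.

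**3. Confounding by nutritional status, true effect zero.** Let m be the undernourished share, rU and rW the complication risks in undernourished and other patients, and sU and sW their probabilities of support.

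- Supported rate = [m·sU·rU + (1−m)·sW·rW] / [m·sU + (1−m)·sW]
- Unsupported rate = [m(1−sU)rU + (1−m)(1−sW)rW] / [1 − m·sU − (1−m)·sW]

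Take m = 0.50, rU = 0.50, rW = 0.25. The last column is the rejection rate of the 5% Chi-square test in 20,000 simulated trials of 150 patients.

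| sU, sW | Supported | Unsupported | Rejects |
|---|---|---|---|
| 0.50, 0.10 | (0.125 + 0.0125)/0.30 = 45.8% | (0.125 + 0.1125)/0.70 = 33.9% | 28% |
| 0.10, 0.30 | (0.025 + 0.0375)/0.20 = 31.2% | (0.225 + 0.0875)/0.80 = 39.1% | 12% |
| 0.20, 0.20 | 37.5% | 37.5% | 5% |

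For m of 0.30 or 0.50 and rU of 0.45 or 0.50, rejection was 17% to 28% when undernourished patients were supported more often (0.50 vs 0.10, or 0.60 vs 0.20). It was 8% to 12% when they were supported less often (0.10 vs 0.30), and 6% to 7% when uptake was nearly equal (0.30 vs 0.20).

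**4. Timing, only if received support includes the postoperative days.** Assume 30% complications and no effect of support.

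- Support completed in 20% without and 10% with a complication: supported 0.03/0.17 = 18%, unsupported 0.27/0.83 = 33%; rejects 30%.
- Complications instead raise the chance of support (40% without, 60% with): supported 0.18/0.46 = 39%, unsupported 0.12/0.54 = 22%; rejects 61%.

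If support is fixed before surgery, neither scenario arises.

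**5. What a by-phase analysis could deliver.** The stepped wedge variance is

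Var = I·s²(s² + T·τ²) / [(IU − W)s² + (U² + ITU − TW − IV)τ²],

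with I = 5, T = 6, U = 15, W = V = 55, so that IU − W = 20 and the last bracket is 225 + 450 − 330 − 275 = 70.

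As a check on the plan's own figure, for the primary outcome: s² = 0.05 × 0.95/5 = 0.0095 and τ² = (0.40 × 0.05)² = 0.0004. Var = 0.0475 × 0.0119/0.218 = 0.002593, SE = 0.0509, and power = Φ(0.15/0.0509 − 1.96) = 83.8%. This matches the stated 84% and uses the control-arm variance.

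For complications, with the variance at the mean rate and 40% vs 20% assumed:

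- s² = 0.30 × 0.70/5 = 0.042.
- CV 0.15: τ² = 0.0036, Var = 0.21 × 0.0636/1.092 = 0.01223, SE = 0.111, power 44%.
- CV 0.40: τ² = 0.0256, Var = 0.21 × 0.1956/2.632 = 0.01561, SE = 0.125, power 36%.
- The 95% interval half-width is 1.96 × 0.111 to 1.96 × 0.125, about 22 to 24 percentage points.

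Other assumed pairs, CV 0.15 to 0.40: 30% vs 15%, 33% to 27%; 30% vs 20%, 16% to 14%; 40% vs 30%, 14% to 12%.

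**The case against.** Complications are one of eight secondary outcomes. The hypothesis and the sample size concern adherence to guidelines, and the primary outcome, screening and care prescription are analysed by GLMM. The morbidity statements are expectations and are not tied to this test. All of that stands, and it limits the severity.

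The unbiased alternative is imprecise at 150 patients. That also stands, but low power is a reason to report an interval, not to substitute a confounded test.

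Three stronger readings are tempting and go beyond the article.

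- A reader might infer that the comparison is reverse-causal, because complications can prevent or trigger support. The analysis sentence speaks of support received, not completed. For patients without malnutrition the listed regimen is preoperative only, and nothing says that a complication triggers artificial nutrition. The mechanism is conditional on how support is defined.
- A reader might infer that supported patients will look worse because the undernourished are treated first. The article does not say who gets support under usual care. It lists immunonutrition for patients without malnutrition too, and it foresees malnourished patients without a prescription. The direction is open.
- A reader might infer that no by-phase analysis of complications exists. The article is condensed, and the word also in the analysis sentence could signal an extra comparison. What can be said is that the article describes only this one.

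**Conclusion.** The concern holds in a limited form and should be fixed. As described, the complication comparison abandons the randomised contrast, adjusts for nothing, and groups patients by a variable linked to nutritional status, center and period. It is confounded in an undetermined direction and cannot show whether the intervention reduces morbidity.

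The size cannot be read from the article. Under the assumed rates above, confounding alone produces spurious gaps of roughly 5 to 12 percentage points when uptake clearly differs by status, with rejection of 8% to 28% instead of 5%. It vanishes if uptake is unrelated to status and the groups are otherwise alike. The timing distortion can be larger, but exists only if support includes the postoperative days. The primary conclusion is not affected.

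**What to change.** State in the analysis section that complications up to 30 days are compared between intervention-phase and control-phase patients, classified by phase at inclusion whatever support they received. Use the GLMM planned for the primary endpoint, with period and intervention as fixed effects and center as a random effect. Report the effect with a 95% confidence interval and say that power is low, so that a non-significant result is not read as no effect.

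If the supported versus unsupported table is kept, present it without a test, label it descriptive and non-causal, and define support, including whether the postoperative days count.

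The cost is wording and one extra model. Patients in both phases are included and followed, complications are already an outcome, and the Trial status section says that data cleaning and analysis had not begun at submission.

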### Ethical considerations

Investigators must recommend that all patients aged 70 years old or over, consulting for a surgery for colorectal cancer, should consider participating in this study. There should be no pre-selection of the patients by the surgeon. The participating patients will give their consent after being told about the study. Their decision to accept or refuse participation will not affect their medical and nursing care.

### Trial status

The enrolment of patients has begun, but data cleaning or analysis had not yet begun as of this article’s submission.

## Discussion

### Discussion of the study design

The ANC study is based on an original methodology, the stepped wedge trial design which differs from the parallel and cross-over designs and presents several advantages. Due to the type of the intervention, the risk of contamination would have been too high with a one to one randomization, hence the need for clusters. The stepped wedge design may require fewer centers than a parallel group design to ensure similar group comparability [30, 31, 40–42].

This type of study design presents benefits with regard to implementation: the sequential introduction of the intervention in all the centers does not disadvantage any particular center. The implementation will be easier and it can facilitate the organization of the study in routine practice [43].

Moreover, the risk of center bias is minimized because each center is its own control and receives the intervention. Therefore, the impact of the intervention can be estimated from both between and within center comparisons [30, 31, 40, 44].

This design also allows an evaluation of the effects of time period on protocol effectiveness (following the temporal evolution of the application of the recommendations in the centers). Centers will differ in the time spent on the intervention. Centers that switch at the first time period will be more experienced with the ANC intervention than centers that switch at last time period [44].

Finally, the stepped wedge design allows each participating center to benefit from the ANC intervention. This opportunity is a motivational factor for taking part in this study. In accordance with good ethical practice, the intervention is expected to do more good than harm.

### Discussion of the intervention

The principal aim of this study is to increase the implementation of the recommendations for perioperative nutritional care for colorectal cancer in elderly patients [19, 20]. In spite of their importance, such recommendations are rarely followed [28, 29]. Our suggestion is that the intervention of the geriatric team (GT) in the perioperative period will help to reduce post-surgical complications and the associated mortality – morbidity. Consequently, the application of the ANC protocol could also lead to a reduction in the length of the post-surgical hospital stay. The ANC study will also develop or strengthen the collaboration between surgical wards and the GT, and the application of actual nutritional recommendations should improve during and after the study.

The introduction of GT in the majority of multidisciplinary hospitals should improve the level of awareness and knowledge of undernutrition-related problems in elderly patients hospitalized for surgery through the training provided by the GT in the wards. It should allow a comprehensive and systematic screening for undernutrition in elderly patients hospitalized for colorectal cancer based on the knowledge of patient weight loss, body mass index, albumin concentration and MNA. It could also promote the application of the good practice recommendations (HAS, ESPEN, SFNEP) and help to develop collaboration and communication among health professionals. Furthermore, in case of severe undernutrition, a specific treatment including artificial nutrition should be discussed in accordance with the recommendations. It is also important to take care of patients with moderate undernutrition in order to prevent the establishment of cachexia.

In summary, the modification of practices induced by the ANC study should allow a decrease in undernutrition-related morbidity and mortality in patients, as well as a decrease in the cost of hospitalization (shortening of the stay and reduction of complications).

Finally, after the completion of the ANC study, the maintenance of the implemented intervention (awareness, collaboration, support, nutritional status diagnosis and nutritional care) and the dissemination of the results will be proposed so that this type of intervention can be extended to other wards and to other types of surgery.

## Abbreviations

ADL: Activity daily life
ANC: *Age Nutrition Chirurgie*
AVS: Analogical visual scale
BMI: Body mass index
GDS: Geriatric depression scale
GT: Geriatric team
IADL: Instrumental activity daily life
MNA: Mini nutritional assessment
SPPB: Short physical performance battery
